### Economic evaluation

The cost of CN on the health system is estimated using standard economic evaluation methodologies. Costings include direct intervention and patient level costs related to hospitalisation and primary care, specialist services and prescribed medications. The costing of health services is based on standard published rates, in particular the Australian Refined Diagnostics Related Group cost weights for hospitalisations, Medicare Benefits Schedule (MBS) charges for medical services and Pharmaceutical Benefits Schedule (PBS) charges for medications. The measure of effect is determined using Quality Adjusted Life Years (QALYs), a measure of life expectancy weighted by health-related quality of life. Average quality of life over the follow-up period for each patient is estimated and weighted by survival to determine QALYs gained post intervention. Incremental cost per QALY gained is calculated between the intervention and control groups.

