## Methods/Design

### Design and study site

The CN study is a single-blind pragmatic RCT of chronically ill patients presenting to the emergency department of Nepean Hospital. Patients are randomly assigned to receive CN (intervention arm) or standard care (control arm). Recruitment is conducted over 10 months, and the two trial arms are followed for 24 months.

Nepean Hospital is a tertiary teaching hospital in Western Sydney, Australia. It provides inpatient and ambulatory services, and averages 580 overnight beds. In 2009–2010 it provided 28,989 overnight admissions and 19,113 day-only admissions. There were 16,562 medical emergency admissions in that year and a total of 51,414 presentations to the emergency department [15].

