### Study variables

In addition to the inclusion and exclusion criteria, six types of variables are collected: demographic and other risk factors, psychosocial, hospital utilisation, community health utilisation, medication usage, and mortality variables. Outcome variables are calculated after 12 months and/or 24 months of follow-up period (Table 1).

**Table 1 T1:** Quantitative data collected in the Care Navigation randomised controlled trial

**Type of data**	**Variables**	**Data source**	**Time of data collection**
**Demographic and risk factor variables**	Age, sex, Indigenous status, marital status	Electronic report from NSW Health database	Baseline.
	Literacy, language, ethnicity, income, education, BMI, living arrangements smoking, alcohol, physical and mental disability, comorbidities	Phone questionnaire-manual data entry	12 months.
**Psychosocial variables**	Quality of life: EQ-5D questionnaire [16]	Phone questionnaire-manual data entry	Baseline, 12 months, 24 months.
	Patient experience: Picker patient experience questionnaire [18]	Mailed paper questionnaire-manual data entry	12 months.
**Hospital utilisation variables**	*For each emergency presentation within the follow-up period:* Triage category, arrival date and time, departure date and time, mode of separation, presenting problem and diagnosis, UDAG status	Electronic report from NSW Health database	24 months.
	*For each hospital admission within the follow-up period:* Arrival date and time, departure date and time, diagnosis related group (DRG), service related group (SRG), investigations conducted	Electronic report from NSW Health database	24 months.
**Community health utilisation variables**	*For each community referral within the follow-up period:* Referral service type, appointment date and time, treatment administered, attendance and transport	Electronic report from NSW Health database	24 months.
**Medication utilisation variables**	Clinical service utilisation (MBS)	Electronic report from Statistics Medicare Australia	24 months.
	Pharmaceutical utilisation (PBS)	Phone questionnaire (manual data entry)	Baseline, 12 months, 24 months.
	Adherence to medications [19]		
**Mortality data**	Date of death	Electronic report from the National Death Index (Australian Institute of Health and Welfare)	24 months.

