### Statistical analysis

Cox proportional hazards models are used to analyse time to first ED presentation, time to first readmission and time to mortality. Readmission rates and length of stay are analysed using Poisson or Negative Binomial models. EQ-5D is analysed using analysis of variance, and t-tests for pairwise comparisons. Baseline characteristics, such as age, gender and severity of illness are examined. Model checking of assumptions and good-of fit tests are conducted for all analyses and further analyses are conducted as required. All analyses are conducted according to the intention-to-treat principle, and will be conducted in SAS v9.3.

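### The QALY comparison names no adjustment for baseline EQ-5D, and the way each patient's quality of life is averaged is left open

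*Protocol article*

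**What the plan says.** The Economic evaluation section gives the QALY construction in one sentence: "Average quality of life over the follow-up period for each patient is estimated and weighted by survival to determine QALYs gained post intervention". The next sentence gives the comparison: "Incremental cost per QALY gained is calculated between the intervention and control groups". Neither says whether the average is a simple mean of visits or is weighted by time, whether the baseline value is one of the values averaged, or whether baseline EQ-5D enters the comparison.

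Table 1 (Study variables) schedules EQ-5D at "Baseline, 12 months, 24 months" and obtains each patient's date of death from the national death register. Under Design and study site: "Recruitment is conducted over 10 months, and the two trial arms are followed for 24 months".

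For EQ-5D as a primary outcome, the Statistical analysis section says "EQ-5D is analysed using analysis of variance, and t-tests for pairwise comparisons", and on covariates only "Baseline characteristics, such as age, gender and severity of illness are examined". Randomisation is stratified by age group and not by quality of life. No numerical target is given for QALYs.

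**The concern.** Cost per QALY is the trial's economic answer, and the QALY difference is its denominator. Two separate matters bear on it.

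- **Baseline.** A patient's utility at entry predicts later utility and, if averaged in, is also part of the QALY itself. With no adjustment, a chance difference between arms at entry shows up as QALYs gained or lost, and variation that baseline could explain stays in the standard error.
- **Averaging.** With three visits 12 months apart, a simple mean and an area under the curve weight the visits differently. The sentence permits both. The choice also matters for patients who die, in a population selected largely for repeated admissions and older age or cardiorespiratory illness.

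**Working it through.** **Inputs from the article.** EQ-5D at 0, 12 and 24 months; 24 months of follow-up; 400 patients after 20% loss, so 200 per arm; a 10-point EQ-5D difference with approximately 80% power at 5%.

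**Assumed, not in the article.** Utility on a 0–1 scale, SD 0.20 to 0.357, equal between-visit correlation r of 0.3 to 0.7, two-sided test.

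**1. The plan's own figure.** None is given for QALYs; the nearest is the EQ-5D power. About 80% power needs 10 / (SD × √(2/200)) = 1.96 + 0.84 = 2.80, so SD = 10 / (2.80 × 0.1) ≈ 35.7 points. The article states no SD, so the figure can be neither confirmed nor refuted. Reading 10 points as 0.10 utility, it supplies the upper SD, 0.357.

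**2. Visit weights over two years, in QALYs per unit of utility.**
- Area under the curve (trapezoid): 0.5, 1.0, 0.5.
- Time-weighted mean × 2 years: 0.5, 1.0, 0.5, which is identical.
- Simple mean of three visits × 2 years: 0.667, 0.667, 0.667.

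For an effect d = 0.10:

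| Effect present at | Simple mean | Area under curve | Simple mean is |
|---|---|---|---|
| 12 months only | 0.067 | 0.100 | 33% low |
| 12 and 24 months | 0.133 | 0.150 | 11% low |
| 24 months only | 0.067 | 0.050 | 33% high |
| Growing linearly from zero | 0.100 | 0.100 | equal |

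In the second row, the same incremental cost gives a cost per QALY 1.50/1.333 = 1.125 times as large.

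**3. Baseline carry-over without adjustment.** The slope of QALYs on baseline utility is:
- Area under the curve: 0.5 + 1.5r = 0.95, 1.25, 1.55 at r = 0.3, 0.5, 0.7.
- Simple mean: 0.667 + 1.333r = 1.07, 1.33, 1.60.

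The standard error of the baseline gap is SD × √(2/200) = 0.020 to 0.036. A gap of 0.05 moves the QALY difference by 0.048 to 0.078 (area under the curve) or 0.053 to 0.080 (simple mean). Changing to area under the curve therefore barely alters the carry-over; only the regression removes it.

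**4. Precision of the area-under-the-curve difference.** In units of SD², the per-patient variance is 1.5 + 2.5r. Adjustment subtracts the squared slope.
- r = 0.3: 2.25 − 0.9025 = 1.3475; ratio of standard errors √(1.3475/2.25) = 0.774, a 23% cut.
- r = 0.5: 2.75 − 1.5625 = 1.1875; ratio 0.657, a 34% cut.
- r = 0.7: 3.25 − 2.4025 = 0.8475; ratio 0.511, a 49% cut.

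At SD 0.25 and r = 0.5 the standard error falls from 0.0415 to 0.0272. The variance ratio 2.75/1.1875 ≈ 2.3 means that, for this comparison, adjustment is worth more than doubling the sample.

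**5. If baseline is left out of the average** (mean of 12 and 24 months × 2), the slope is 2r = 0.6 to 1.4 and the cuts are smaller: √((2 + 2r − 4r²)/(2 + 2r)) = 0.93, 0.82, 0.65, or 7%, 18% and 35%. Carry-over shrinks but remains.

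**6. Deaths.** Illustration: utility 0.6 at entry, 0.4 at 12 months, death at 18 months.
- Simple mean × survival: 0.5 × 1.5 = 0.75.
- Area under the curve, last value held to death: 0.5 + 0.4 × 0.5 = 0.70.
- Area under the curve, falling linearly to zero at death: 0.5 + 0.5 × 0.4 × 0.5 = 0.60.

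The simple mean exceeds both because it averages away the decline. With a flat 0.6 and 0.6 it gives 0.90, the same as the held-level area; falling to zero gives 0.75. The rule between last visit and death therefore matters even with area under the curve.

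**The case against.** The strongest reply is that the article states no wrong formula. A time average over a period, multiplied by time survived, is the area under the curve, and the section appeals to standard economic methods. This stands. A reader might infer that the plan uses the unweighted mean of three visits and so misstates QALYs by 11% to 33%. The text does not say that, and the error vanishes for an effect that grows linearly from zero. Nor is the trapezoid the truth: if benefit begins soon after randomisation, the real gain approaches 2d and 1.50d is itself low.

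A reader might also infer that an unadjusted comparison is biased. Under randomisation it is not biased in expectation. The cost is error conditional on the imbalance that happens to arise, and a wider interval.

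Third, a condensed article may leave covariates, missing visits and the rule up to death to a fuller plan. So silence is weak evidence that no adjustment is intended, and the article does not exclude it. But this section does fix how QALYs are built and compared, and the Statistical analysis section names an EQ-5D method without a baseline covariate, saying only that baseline characteristics are examined.

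Finally, QALYs are neither a primary nor a listed secondary outcome. That limits the weight of the point but does not remove it, since cost-effectiveness is a stated study objective.

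**Conclusion.** The point holds in a limited form. As written, the QALY comparison carries no stated adjustment for a baseline measure that the trial collects. For assumed correlations of 0.3 to 0.7, each unit of chance baseline gap moves the QALY difference by about 0.95 to 1.6. Adjustment would reduce the standard error of the area-under-the-curve difference by about 23% to 49%. These figures assume equal between-visit correlation and complete visits, with baseline part of the QALY; the percentage cuts do not depend on the SD.

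The weighting problem is conditional. It arises only if the average is a simple mean of the visits, and then ranges from none to a third of the QALY gain depending on when the effect occurs, with too much credit for patients who decline before dying. The two matters are independent: area under the curve settles the weighting, and regression settles the baseline gap. It is worth correcting before analysis, but it is not an error that invalidates the economic evaluation.

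**What to change.** In the Economic evaluation section, or in the analysis plan that governs it, state that:

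- each patient's QALYs are the area under the EQ-5D utility curve over 24 months, linear between visits, with a named rule between the last visit and death (for example, last value held) and zero from the date of death;
- the between-arm QALY difference, which is the denominator of the cost per QALY, is estimated by regression adjusted for baseline EQ-5D utility.

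Reporting a second rule for the interval before death would show how far the result depends on it. The change costs wording only: the three EQ-5D assessments and the date of death are already collected, and neither sample size nor visit schedule is affected.

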### Process evaluation

A process evaluation is conducted to describe the organisational setting and context within which CN is developed and implemented. Interviews are carried out with individuals at several levels of program implementation using purposive sampling as follows: a) hospital, Local Health District and NSW Ministry of Health policy and decision makers; b) Nepean Hospital staff in key roles to explore details and processes of CN, as well as barriers and facilitators to its implementation; c) clinical staff with daily indirect involvement with CN to provide broader organizational context; and d) patients in the intervention arm, focusing on their experience of chronic illness and its management as a result of CN. Paired interviews are carried out with patients, their carers, and also the patient’s GP, where possible.

All interviews are recorded and transcribed verbatim. Analysis is thematic, and NVivo v9 is used to assist with data management. Coding is carried out inductively based on the themes that emerge from interviews.

### Ethics

Ethics approval was received from Sydney West Area Health Service Human Research Ethics Committee – Nepean Campus [AU RED: HREC/09/NEPEAN/55], now Nepean Blue Mountains Local Health District Human Research Ethics Committee.

## Discussion

To our knowledge, this is the first study to provide a mixed-method evaluation of the implementation and effectiveness of a care coordination program in Australia that includes a heterologous population and substantial follow-up period. Evidence of any improved patient outcomes and satisfaction due to care coordination are critical, given recent interest by governments. Coordinated care is becoming incorporated at the national policy level in several countries [11,12,17]. The integration and continuity of prevention and care is a priority action area in the National Chronic Disease Strategy of Australia [17]. These policy initiatives must be underscored by a solid evidence-base.

The main strengths of this study are the nature of the CN intervention, the comprehensive process evaluation, and the design of the RCT. The quantitative components of the study utilise a *pragmatic* RCT, allowing heterologous patient groups to be randomised to receive interventions that can be tailored to individual patients based on type, complexity and severity of disease, while still providing statistically meaningful information. The intervention identifies patients in the acute setting with a single point of access, involves GPs, builds capacity within the ED, and places the patient at the centre of decision making using a systems approach to the delivery of health care. A patient-centred focus is essential to ensure the health care and social needs of the population are adequately met [5,7].

The CN process evaluation provides qualitative data to complement outcome measures collected by the trial. If significant changes in patient and health service outcomes are observed, the process evaluation describes the mechanisms underpinning these changes. An account of the implementation of the intervention, and the context of the health system it is conducted within, gives a richer understanding of the intervention and enhances the external validity of the RCT.

The design of the RCT incorporates a large sample size with adequate power to detect the primary outcomes, and a long follow-up period to observe meaningful improvements in patient health outcomes [18,19]. The use of independent random assignment to the intervention, blinding where feasible, and an intention to treat analysis minimises bias.

The main challenges of the intervention are loss to follow-up, heterogeneity of the intervention received between patients, and bias in patient recruitment. Loss to follow-up is minimised by receiving consent at baseline for hospital, medication and death data to be obtained electronically from local and national health databases for the entire follow-up period. Patients are also in regular contact with CN nurses during the period of follow-up to action care plans, however, follow-up data collection is not conducted by CN nurses to minimise bias. The intervention is conducted with consistent protocols to minimise between-patient variability. Care Navigation nurses are trained in these protocols, and intervention delivery checklists are used to record intervention delivery to the patients. To minimise bias in patient recruitment, eligibility criteria are designed to capture all patients who would normally receive CN upon presentation to the emergency department, while still maintaining accuracy and completeness of the data. Efforts are made to accommodate culturally and linguistically diverse patients.

This mixed-methods study informs the generalisability and sustainability of care coordination programs in Australia and internationally. The CN trial aims to build upon these principles to provide a comprehensive coordinated care program for improving health outcomes among patients with chronic illness.

## Abbreviations

EQ-5D: Euroqol quality of life questionnaire; GP: General practitioner; MBS: Medical benefits schedule; OECD: Organisation for economic co-operation and development; PBS: Pharmaceutical benefit scheme; QALY: Quality adjusted life years; RCT: Randomised controlled trial.
